#### 4.1.2 Study Population

The sample in this study is to be drawn from a target population of stable, type 2 diabetic patients. Satisfying the inclusion and exclusion criteria, these patients will constitute a recognizable and identifiable group as they will specifically

- Have a documented diagnosis of type 2 diabetes mellitus according to the American Diabetes Association,
- Demonstrate stable type 2 diabetes mellitus for at least 3 months prior to study entry,
- On stable diabetes treatment regimen (oral hypoglycemics with or without insulin) for at least 2 months prior to screening,
- Have screening HbA1c <10.0%,
- Have a Body Mass Index between 25 and 38 add kg/m^2, and
- Will not have used oral or parenteral glucocorticoids for at least 30 days prior to screening.

#### 4.1.3 Statistical Model/Design

The study design is that of a multicenter, double-blind, placebo-controlled, parallel group evaluation of the effects of two doses of TH9507 over 12 weeks. Serial determinations will be

assessed using a repeated measures parallel group design.

#### 4.1.4 Null and Alternative Hypotheses

The null hypothesis is that each active dose does not result in a change in the relative insulin response over the 12-week treatment period. The alternative hypothesis is that at least one of the two doses of TH9507 or placebo produces a change in the primary endpoint over the 12-week treatment period. Thus the primary analysis is two-sided since the direction of the putative difference is not specified.

Assessment of these hypotheses may be conducted by comparing the changes from baseline at Week 12 across the three treatment groups (including placebo) using a repeated measures ANOVA model including a treatment effect and a random time effect and adjusting for possible effects of investigational site and insulin use. Due to the size of this study relative to the number of factors under consideration, F-tests for main effects (treatment, insulin use, center, time) will be constructed ignoring possible interactions. Comparisons of active treatment group relative to placebo may be performed using a two-sided alternative.

In a secondary analysis, paired t-tests will be used to compare the baseline (Week 0) and Week 12 values of HbA1c for each treatment group. Additionally, a repeated measure analysis, including terms for the fixed effects, treatment, insulin use, and center, and the random effect:time, may be implemented to assess change from baseline in HbA1c over the 12-week treatment period.

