## 1.1 Rationale

The clinical development program for TH9507 includes its use in patients who could benefit from enhancement of anabolic effects, including patients with COPD, hip fractures, and other age-related disorders associated with somatopause. As noted, different changes in insulin sensitivity have been observed with rhGH and GRF analogue administration. It is anticipated that a number of patients to be enrolled in future trials of TH9507 will have glucose intolerance and/or overt diabetes. Therefore, the purpose of this study is to investigate the safety of daily administration of TH9507 in patients with type 2 diabetes mellitus, in particular, the potential for effects on insulin sensitivity and diabetic control.

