## 2. Study Objectives

The primary objective will be to evaluate the safety of two doses of TH9507 administered over 12 weeks by daily subcutaneous injections in patients with stable type 2 diabetes.

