#### 4.1.5 Sample Size Estimation

Available trial data from each subject who received at least one dose of study medication will be used in the primary safety analysis. Using PASS2000 (NCSS Software), a total of 45 subjects (15 per group) will be enrolled into the study to ensure that approximately 39 subjects (13 per group) complete the study under the following sample size assumptions:

- A parallel group design is employed, with equal randomization between the groups.
- The primary endpoint is relative insulin response over time.
- The comparison is made using a Type I error rate of 0.05.
- The comparison is assessed using a Type II error rate of, at most, 0.2 which provides a minimum power to detect the specified difference 80%.
- An F-test from a repeated measures ANOVA model including a fixed treatment effect and a random effect for time is used to test the null hypothesis of no treatment difference.
- The baseline value for the placebo group is 0.23. A 15% difference is expected in each of the treatment groups. A constant standard deviation of 0.20 is expected.
- The relative insulin response is calculated at baseline, week 1, week 4, week 8, and week 12.

Similar calculations suggest that a sample size of 13 subjects per group will be sufficient to detect a 5% change from baseline in HbA1c for each treatment group (including placebo) at week 12 under the following sample size assumptions:

- Each comparison is made using a Type I error rate of 0.05.

- Each comparison is assessed using a Type II error rate of, at most, 0.2 which provides a minimum power to detect the specified difference 80%.
- An effect size of 1 is expected.
- A paired t-test is used to test the null hypothesis of no treatment difference.

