### 4.1.13 Multiple Significance Testing

Unless otherwise specified, all p-values will be reported to four decimal places using two-sided tests of significance with no correction for multiplicity (multiple outcomes or multiple comparisons) having been employed. Statistical significance will be assessed at the conventional level of 0.05 in all cases unless otherwise stated, and thus any significant findings for parameters other than the primary endpoint must be interpreted accordingly.

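### The glycaemic safety question rests on two-sided 0.05 tests of no change, and on the primary endpoint a non-significant result could not support absence of harm

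*Protocol*

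**What the plan says.** Section 2 gives one objective: "The primary objective will be to evaluate the safety of two doses of TH9507 administered over 12 weeks". Section 4.1.1 repeats it and adds that the evaluation is relative to placebo. Section 1.1 explains the interest, "in particular, the potential for effects on insulin sensitivity and diabetic control", because later trials of TH9507 are expected to include patients with glucose intolerance or diabetes.

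The inferential rules are in section 4:

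- **Primary endpoint (4.1.4).** "The null hypothesis is that each active dose does not result in a change in the relative insulin response over the 12-week treatment period". The section adds: "Thus the primary analysis is two-sided since the direction of the putative difference is not specified". A repeated measures comparison of the three groups, and comparisons of each dose with placebo, are described as things that may be done.
- **HbA1c (4.1.4).** Paired t-tests of Week 0 against Week 12 within each arm will be done. A repeated measures model with a treatment term is optional.
- **Sample size (4.1.5).** The F-test for the primary endpoint and the paired t-test for HbA1c are each one that "is used to test the null hypothesis of no treatment difference".
- **Significance (4.1.13).** "Statistical significance will be assessed at the conventional level of 0.05 in all cases unless otherwise stated", without correction for multiplicity.

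Section 4 mentions no confidence interval and no limit of acceptable worsening. Section 4.1.9 bases the safety assessment mainly on adverse-event frequency and out-of-range laboratory counts, with shift tables and descriptive summaries. Section 4.1.1 adds dose adjustments and the number of subjects whose diabetes control changes.

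**The concern.** When the question is whether a drug worsens insulin response or glycaemic control, the reassuring answer is that any worsening is small. A test of no difference cannot give that answer. It can reject, which shows an effect, or fail to reject, which becomes more likely as the sample shrinks or the data get noisier. Only an estimate against placebo with an interval separates a harm that has been excluded from one the study was too small to see.

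At stake is the use named in section 1.1: informing the inclusion of diabetic patients in later trials. If the primary result is a p-value above 0.05, the protocol gives the reader no stated means of judging how large a worsening remains possible. For HbA1c, the test committed to in section 4.1.4 does not involve placebo at all, although the objective is comparative.

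**Working it through.** **Inputs from section 4.1.5:** placebo baseline 0.23; expected difference 15%; SD 0.20; five measurements (baseline, Weeks 1, 4, 8, 12); 13 completers per arm; two-sided 0.05; power at least 80%. For HbA1c: 5% change from baseline, effect size 1, paired t-test. **Not given:** the within-subject correlation ρ, which is varied below.

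**1. The plan's own power figure (primary endpoint).** A 15% difference is 0.15 × 0.23 = 0.0345. For the between-group F-test on the subject mean of five visits:

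- SD of the mean = 0.20 × √((1 + 4ρ)/5)
- With both doses shifted by 0.0345, the squared deviations of the three group means sum to 0.0345² × 2/3 = 0.0007935
- Noncentrality λ = 13 × 0.0007935 / SD²; degrees of freedom 2 and 36; critical F = 3.26

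| ρ | SD of mean | λ | Power |
|---|---|---|---|
| 0 | 0.089 | 1.29 | 15% |
| 0.5 | 0.155 | 0.43 | 8% |
| 1 | 0.200 | 0.26 | 7% |

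The stated 80% is not reproduced. Doses shifting in opposite directions give 11% to 37%. Using the mean post-baseline change instead (SD = 0.20 × √(1.25(1 − ρ))) gives 8% at ρ = 0.5, 13% at 0.8, 22% at 0.9 and 79% at 0.98, so only a near-perfect correlation rescues the figure. Reading 15% as an absolute 0.15 does reach 80% at ρ of about 0.33, but that is 0.15/0.23 = 65% of baseline.

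**2. What a non-significant primary result would leave open.** For dose minus placebo in Week 12 change:

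- SD of change = 0.20 × √(2(1 − ρ))
- Half-width = t(0.975, 24) × SD × √(2/13), with t = 2.064 and √(2/13) = 0.392

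| ρ | SD of change | Half-width | As % of 0.23 | Pairwise power at 0.0345 |
|---|---|---|---|---|
| 0 | 0.283 | 0.229 | 100% | 6% |
| 0.5 | 0.200 | 0.162 | 70% | 7% |
| 0.8 | 0.126 | 0.102 | 45% | 10% |

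The half-width is about 3 to 7 times the 0.0345 the study was planned to detect (0.102/0.0345 to 0.229/0.0345).

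**3. HbA1c at the stated effect size of 1.**

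- Within arm: noncentrality √13 = 3.61 on 12 degrees of freedom gives 91% power. Ten subjects would give 80%, so the claim that 13 suffice holds.
- Between arms: noncentrality 1/√(2/13) = 2.55 on 24 degrees of freedom gives 69% power.

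A change of that size would be found more often than missed.

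**4. Would an HbA1c margin of 5% work?** An effect size of 1 for a 5% change implies an SD of change of 5% of baseline. The chance that a one-sided 95% upper bound excludes a 5% worsening when there is none is then 80%. Assuming instead a baseline of 8% (margin 0.4 points) and an SD of change of 0.6, 0.8 or 1.0 points, the chance is 50%, 34% or 26%.

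**The case against.** The strongest reply is that the protocol contains no rule equating non-significance with safety. Its verbs are investigate and evaluate, the test is open in direction, and a 15% difference is expected, so the trial can fairly be described as looking for an effect either way. That stands. A reader might infer that the trial is set up to declare the drug safe when p > 0.05; no section says so. The narrower point remains: the protocol states no other inferential reading of its primary endpoint.

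A reader might also infer that glycaemic safety is judged by these tests alone. Sections 4.1.1 and 4.1.9 contradict that: out-of-range counts, shift tables, dose adjustments and changes in diabetes control also count. None of them, however, bounds the size of a harm relative to placebo.

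A third tempting reading is that a relevant HbA1c harm would usually be missed. At the protocol's own effect size it would not. It becomes so only under a larger SD of change, which the protocol does not give.

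Section 4.1.9 also promises analysis of variance, between and within regimens, for biochemical laboratory parameters labelled as secondary endpoints. It does not name HbA1c but could be read to cover it. That would supply a comparison with placebo, still judged at 0.05.

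Finally, intervals are often left to the analysis plan, which is not at hand and may contain them. Their absence alone would be no finding. The hypotheses, the within-arm HbA1c test and the significance rule, however, are fixed in this protocol.

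**Conclusion.** The point holds in a limited form. The objective is comparative safety, but the stated inference on relative insulin response and HbA1c is two-sided testing of no change, with comparisons against placebo optional in section 4.1.4. On the primary endpoint, power of about 7% to 15% for the planned 15% difference, and an interval half-width of about 45% to 100% of baseline, mean that a non-significant result cannot support absence of harm.

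These figures rest on reading 15% as relative to 0.23, on both doses shifting alike, and on correlations assumed at 0 to 1 for power and 0 to 0.8 for the interval. The half-widths are for a single-visit change score without covariate adjustment. The size of the problem is confined to the primary endpoint; for HbA1c the defect is the choice of comparison, not the power at the stated effect size.

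A formal HbA1c non-inferiority rule is not required. In particular, 5% should not become the margin by default: section 4.1.5 gives it as a detectable within-arm change, not a tolerable harm. Moreover, section 3.4.4 lets investigators adjust insulin and oral hypoglycaemics, so HbA1c could stay within a margin because background therapy was raised.

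**What to change.** Before unblinding, amend sections 4.1.4 and 4.1.13 to:

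1. Commit to reporting, for each dose, the dose-minus-placebo difference in change from baseline at Week 12, with its 95% confidence interval, for both relative insulin response and HbA1c, from the planned model adjusted for site and insulin use.
2. Base the glycaemic safety interpretation on those intervals, read together with changes in antidiabetic medication by arm.
3. State that p > 0.05 will not be described as absence of an effect.

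The within-arm paired t-tests can stay as supporting description. If the sponsor wants an HbA1c margin, it should be fixed before unblinding and justified as an acceptable worsening, with the chance of meeting it shown over a range of SDs.

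The cost is wording, with no extra patients, visits or assays. The small downside is that the intervals, especially for relative insulin response, will be wide, so the safety statement will read less favourably than a non-significant p-value might.

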## 4. Statistical Methods

### 4.1 Statistical Methods to be Employed

#### 4.1.1 Study Objectives

This is a Phase II, placebo-controlled, comparative study. The primary objective is to evaluate the safety of two doses (1 mg and 2 mg by daily subcutaneous injection) of TH9507 relative to placebo administration, over a 12-week period in patients with stable, type 2 diabetes.

The primary endpoint is the change in relative insulin response following the oral ingestion of glucose over the 12-week treatment period. The relative insulin response is defined as the ratio of the incremental plasma insulin response above basal at 30 minutes to that of plasma glucose, divided by basal plasma insulin levels.

The secondary objectives are to evaluate the effects of 12 weeks of daily treatment with TH9507 on HbA1c, blood glucose measurements, **use of oral hypoglycemic agents and/or insulin and control of diabetes.**

The secondary endpoints include the change in HbA1c at Week 12 compared to baseline and changes in mean daily serum glucose concentrations compared to the 14 day lead-in period values, **changes in the number of dose adjustments per week for insulin and/or oral hypoglycemic agents compared to the 14 day lead-in period, and the number of subjects with a change in the control of diabetes.**

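### Section 4.1.4 states the primary hypotheses as within-arm changes that overlap and do not match the placebo-controlled objective or the between-arm test meant to assess them

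*Protocol*

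**What the plan says.** Protocol 4.1.1 gives the objective as the safety of two doses "of TH9507 relative to placebo administration, over a 12-week period in patients with stable, type 2 diabetes". The main outcome named there is how relative insulin response changes during treatment.

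Protocol 4.1.4 then states the hypotheses:

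- Null: "The null hypothesis is that each active dose does not result in a change in the relative insulin response over the 12-week treatment period". Placebo is not mentioned.
- Alternative: "The alternative hypothesis is that at least one of the two doses of TH9507 or placebo produces a change in the primary endpoint". Placebo is now included.

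The same section says that these hypotheses may be assessed by "comparing the changes from baseline at Week 12 across the three treatment groups (including placebo) using a repeated measures ANOVA model". It adds that "F-tests for main effects (treatment, insulin use, center, time) will be constructed ignoring possible interactions", and that "Comparisons of active treatment group relative to placebo may be performed using a two-sided alternative".

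Protocol 4.1.5 bases the sample size on an F-test from a repeated measures model which "is used to test the null hypothesis of no treatment difference".

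**The concern.** The hypotheses define what a significant or non-significant primary result allows the report to say. Here they describe change over time inside an arm, whereas the objective, the named comparison and the sample size all concern differences between arms. The null covers two arms and the alternative covers three, so they do not divide the possibilities between them.

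This matters in this trial because a shift common to all arms is plausible. Every subject keeps a diary of diet, exercise and home glucose (3.2, 3.5.1), and insulin and oral hypoglycemic doses may be adjusted at the investigator's discretion (3.4.4). Such a shift would make the stated alternative true without any effect of TH9507. Both the between-arm assessment and the active-versus-placebo comparisons are also worded as optional. After unblinding, the text could therefore be cited in support of either a within-arm or a between-arm primary claim.

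**Working it through.** **1. The statements side by side**

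| Place | Statement | Type |
|---|---|---|
| 4.1.1 objective | each dose relative to placebo | between arms |
| 4.1.4 null | no change on either active dose | within arm, two arms |
| 4.1.4 alternative | change on a dose or on placebo | within arm, three arms |
| 4.1.4 test | changes compared across three arms | between arms |
| 4.1.5 null | no treatment difference | between arms |

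Write the mean changes as P (placebo), D1 and D2. The stated null is D1 = D2 = 0. The stated alternative is that at least one of P, D1 and D2 is not 0. With D1 = D2 = 0 and P not 0, both hold. The treatment F-test has a third null, P = D1 = D2.

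**2. Inputs**

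- From 4.1.5: 13 completers per arm, SD 0.20, level 0.05, placebo baseline 0.23, a 15% difference, and five visits.
- 15% read as relative is 0.15 × 0.23 = 0.0345. Read as absolute it is 0.15.
- Assumption: within-subject correlation r from 0 to 0.9, because the protocol gives none.
- SD of change = 0.20 × √(2(1 − r)): 0.283 at r = 0, 0.200 at r = 0.5, 0.089 at r = 0.9.
- Critical value of F with 2 and 36 degrees of freedom: 3.26.

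**3. The plan's own figure**

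Section 4.1.5 claims at least 80% power with 13 per arm. With both doses differing from placebo by d, the noncentrality is λ = 13 × (2/3) × d²/V. Here V = 0.04 for a single measure, or 0.04/5 = 0.008 for the mean of five uncorrelated visits.

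- d = 0.0345: λ = 0.26 to 1.29, power 6.8% to 15.0%.
- d = 0.15: λ = 4.9 to 24.4, power 46% to 99%.

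The 80% is not reproduced on the relative reading. On the absolute reading it depends on a correlation that is not stated. That is a separate matter, and the present point does not rest on it.

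**4. Shift common to all arms**

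P = D1 = D2 gives λ = 0, so the treatment F-test rejects exactly 5.0% of the time for any size of shift and any r. The stated alternative is true and there is no drug effect. In simulation at r = 0.5 to 0.8, the separate time F-test rejects 16% to 35% of the time for a shift of 0.0345 and over 99% for 0.15.

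**5. Change on placebo only**

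λ = 13 × (2/3) × d²/(SD of change)².

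| d | r = 0 | r = 0.5 | r = 0.9 |
|---|---|---|---|
| 0.0345 | λ 0.13, rejects 5.9% | λ 0.26, rejects 6.8% | λ 1.29, rejects 15.0% |
| 0.15 | λ 2.44, rejects 24.9% | λ 4.88, rejects 45.9% | λ 24.4, rejects 99.2% |

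The stated null is true throughout this table, and so is the stated alternative. Both doses differ from placebo, so rejection is the right answer to the objective.

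**6. The two contrasts without adjustment**

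Under no effect, two dose-placebo tests at 0.05 each, sharing one placebo arm of 13, give at least one false positive in about 9% of simulated trials.

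**The case against.** The strongest reply is that the operative text is already between-arm. The objective, the comparison in 4.1.4 and the null in 4.1.5 agree with one another, and only two sentences do not. This stands: the planned test suits the objective, and the fault lies in the hypotheses.

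A charitable reader might also take a change resulting from a dose to mean a change relative to placebo. That reading does not survive the alternative, which names placebo among the treatments able to produce a change.

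A reader might infer four stronger things, none of which the protocol supports:

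- *The F-test lacks power when all arms shift together.* Rejecting 5% of the time is correct when the drug does nothing. The listed time F-test can pick up a common shift, although 4.1.4 does not tie it to the hypotheses.
- *The F-test inflates the Type I error when only placebo changes.* The stated alternative is also true there, and the doses do differ from placebo, so this is not a clean Type I error.
- *A significant F-test need not mean that either dose differs from placebo.* As hypotheses, equality of three arms is the same as both doses equalling placebo. In a given sample F may be significant with neither contrast significant, but this is frequent (about 16.5% of trials) only if the doses act in opposite directions, for example +0.5 and −0.5 SD. If both act at +0.5 SD it is 0.3%.
- *Two primary contrasts must replace the F-test.* That is a design preference. With no multiplicity correction, as 4.1.13 states, it would raise the chance of a false positive to about 9%.

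Whether contrasts are optional is often settled in an analysis plan. Here, though, the option sits beside wrongly stated hypotheses, so it should be settled with them.

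**Conclusion.** The point holds as an error in the stated primary hypotheses. They overlap, describe within-arm change, and contradict the objective, the named test and the sample-size null. It does not show that the planned F-test is invalid.

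The overlap and the 5% rejection under a common shift follow from the wording and from zero noncentrality, and need no assumed effect size. The placebo-only figures, 6% to 15% and 25% to 99%, rest on SD 0.20, 13 per arm, shifts borrowed from the two readings of the 15% in 4.1.5, and an assumed correlation of 0 to 0.9. They show how far the stated null and the test can part, and are not error rates of the trial. The correction should be made, because it changes what the trial may conclude and costs little.

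**What to change.** Rewrite 4.1.4 as follows:

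- **Null:** mean change from baseline to Week 12 in relative insulin response is equal in the three arms.
- **Alternative:** at least one TH9507 dose differs from placebo, in either direction. This is the exact complement of the null. Remove the reference to a change produced by placebo.
- **Primary test:** keep the three-arm treatment F-test, as 4.1.5 names it, and make the between-arm assessment mandatory.
- **Contrasts:** make 1 mg minus placebo and 2 mg minus placebo mandatory, reported with confidence intervals and with multiplicity controlled, for example by Dunnett's method or by testing them only after a significant F-test. Amend 4.1.13 to match.
- **Within-arm change from baseline:** label it as descriptive.

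The cost is wording. The data, visits, model and number of subjects are unchanged by this point, and the F-test remains the basis of the sample size. The one drawback is slightly less power for the individual contrasts than if they were left unadjusted.

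### The only HbA1c test that the protocol firmly names and sizes is a within-arm paired t-test, which section 4.1.5 mislabels as a test of treatment difference; the dose-versus-placebo contrast should decide.

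*Protocol*

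**What the plan says.** Section 4.1.1 frames the objective as safety relative to placebo and lists the change in HbA1c at Week 12 among the secondary endpoints.

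Section 4.1.4 then commits to a test for HbA1c by name: "paired t-tests will be used to compare the baseline (Week 0) and Week 12 values", separately for each treatment group. It adds a repeated measures model with treatment, insulin use and center as fixed effects, but only as something that may be done.

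Section 4.1.5 states that "a sample size of 13 subjects per group will be sufficient to detect a 5% change from baseline in" HbA1c, and that this applies "for each treatment group (including placebo) at week 12 under the following sample size assumptions". The assumptions include "Each comparison is made using a Type I error rate of 0.05", power of at least 80%, and "An effect size of 1 is expected". The last one reads "A paired t-test is used to test the null hypothesis of no treatment difference".

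Section 4.1.9 has a general rule: changes from baseline in biochemical laboratory parameters, tagged there as secondary endpoints, will be analyzed by ANOVA with comparisons both between and within regimens. Section 4.1.13 sets testing "using two-sided tests of significance with no correction for multiplicity".

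**The concern.** A paired t-test inside one arm has as its null that the mean change in that arm is zero. It says nothing about whether a dose differs from placebo. Section 4.1.5 nevertheless attaches the label of no treatment difference to it. Taken literally, a significant change in an active arm would be reported as a treatment difference.

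The natural way to bring placebo in is to set the three paired p-values side by side, and that is not a valid test of the difference. If all arms drift together, one active arm can cross 0.05 by chance while placebo does not, which gives a false signal. If placebo improves and an active arm stays flat, the flat arm's non-significant result gives false comfort. The second error matters in a trial meant to detect harm to diabetic control.

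The sample-size statement follows the same test, so its 80% does not describe sensitivity to a difference from placebo.

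**Working it through.** **Inputs from the protocol.** 13 completers per group, effect size 1, two-sided 0.05 per comparison, power at least 80% (4.1.5 and 4.1.13). No SD for HbA1c change is given, so everything below is in units of the SD of change, and the 5% change cannot be checked against the effect size of 1.

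**1. The plan's own figure.** Paired t-test: df = n − 1, noncentrality = d√n.

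- n = 13, d = 1: noncentrality √13 = 3.61, df 12, power 91.1%.
- n = 10, d = 1: power 80.3%, so 10 is the minimum for 80%.
- At n = 13, 80% power is reached at d = 0.85.

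The claim that 13 is sufficient reproduces, for change within one arm.

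**2. Reading paired tests across arms.** Assume no drug effect, independent arms, and the same shift d in all three. Let p be the power of one paired test at n = 13.

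- At least one active arm significant: 1 − (1 − p)².
- At least one active arm significant and placebo not: [1 − (1 − p)²](1 − p).

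| Shared shift (SD) | p | At least one active | At least one active, placebo not |
|---|---|---|---|
| 0.25 | 13.2% | 24.7% | 21.4% |
| 0.5 | 38.2% | 61.8% | 38.2% |
| 0.75 | 70.0% | 91.0% | 27.3% |
| 1 | 91.1% | 99.2% | 8.9% |

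For d = 0.5: (1 − 0.618²) × 0.618 = 0.382. With q = 1 − p the last column is q − q³, which peaks at q = 1/√3 with value 0.385. The 38% is therefore close to the worst case over all shifts.

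**3. Sensitivity against placebo, unadjusted.** Two-arm t-test on change: df = 2n − 2 = 24, noncentrality = d√(n/2).

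- n = 13, d = 1: noncentrality √6.5 = 2.55, power 68.7%.
- 80% power at n = 13 needs d = 1.15; at d = 1 it needs 17 per group (80.7%).

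Carrying the effect size of 1 over to this contrast is an assumption made here.

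**4. Sensitivity against placebo, baseline-adjusted.** Assume equal variances at baseline and Week 12, with correlation ρ. The SD of change is σ√[2(1 − ρ)] and the residual SD after adjustment is σ√(1 − ρ²). Their ratio, residual to change, is k = √[(1 + ρ)/2]. A difference of d SD of change becomes d/k residual SDs. With error pooled over three arms, df = 39 − 3 − 1 = 35, before terms for stratum and center.

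| ρ | k | Power at 1 SD of change | Difference at 80% power |
|---|---|---|---|
| 0.3 | 0.806 | 87% | 0.91 SD |
| 0.5 | 0.866 | 82% | 0.98 SD |
| 0.7 | 0.922 | 77% | 1.04 SD |

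**The case against.** The strongest reply is that a between-arm analysis is already promised. Section 4.1.9 uses firm language for an ANOVA comparing regimens on laboratory secondary endpoints, and HbA1c change is a secondary endpoint. This stands in large part: a reader might infer from 4.1.4 alone that no comparison with placebo is planned, and the protocol does not support that. Coverage is not certain, however. Section 3.5.2.3.5 lists HbA1c under special tests rather than blood chemistry, and 4.1.9 says that special tests will be considered as appropriate. Nor is that ANOVA named as deciding the HbA1c conclusion.

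Placebo also gets its own paired test, so a large shared shift would usually be visible: at 1 SD, placebo is itself significant 91% of the time. That is true, and it is why the last column of the first table falls to 9% there. It does not turn a comparison of p-values into a test.

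Two other inferences are tempting and fail. One is that the protocol claims 80% power against placebo and delivers 69%. It makes no such claim; its 80% is for change within a group, and the shortfall largely disappears under baseline adjustment. The other is that sizing the placebo arm for a 5% change shows that the sponsor expects placebo to drift. Section 4.1.5 mainly states what could be detected. Discretionary adjustment of diabetes medication (3.4.4) is a possible source of a common shift, but the protocol predicts none.

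Finally, HbA1c is secondary, the primary endpoint is relative insulin response, and 4.1.13 advises caution beyond the primary endpoint. That limits the weight of the point. The caution concerns multiplicity, though, not the choice of contrast.

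**Conclusion.** The point holds in a limited form. The protocol states the wrong null for the paired t-test. The only HbA1c-specific test that it commits to, and the only one that its HbA1c sample size covers, is within-arm, although the objective is relative to placebo. The between-arm routes are optional (4.1.4) or general and not named as decisive (4.1.9).

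If the paired tests are read across arms, a spurious contrast between active and placebo appears in 9% to 38% of trials. This assumes no drug effect, independent arms, 13 completers per arm and a shared shift of 0.25 to 1 SD. These shifts are illustrative, and the upper figure is near the maximum of 38.5%.

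This should be corrected, but it is a secondary-endpoint issue and does not touch the primary analysis.

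**What to change.** In 4.1.4, name the Week 12 HbA1c contrast of each dose with placebo as the deciding HbA1c analysis, adjusted for baseline HbA1c, insulin-use stratum and center, and reported with a 95% CI. Keep the within-arm paired changes as description. State in 4.1.9 whether HbA1c falls under the general ANOVA, so that the two sections agree.

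In 4.1.5, restate the null of the paired test as no change from baseline within the group, and say that the 80% applies only to that change. Then give the between-arm sensitivity for the model actually chosen, with its assumptions. At 13 per group and 80% power, this is about 1.15 SD of change for an unadjusted two-arm t-test, or roughly 0.9 to 1.05 SD with baseline adjustment and three-arm pooled error at a baseline-to-Week 12 correlation of 0.3 to 0.7. The 1.15 SD figure should not be paired with the adjusted model.

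The cost is protocol and analysis-plan wording, with no added subjects, visits or assays. The stated HbA1c sensitivity becomes somewhat less favourable than the 0.85 SD detectable within one arm.
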